## **Appendix 2: Other Local Tolerability Scoring**

### **Bruising Extent**

The treatment area will be assessed for bruising

Grade Description:

- 0 NONE No visible bruising around treatment area
- 1 MILD 0 to 2cm bruising around treatment area
- 2 MODERATE 2 to 5 cm bruising around treatment area
- 3 SEVERE Greater than 5 cm bruising around treatment area

### **Itching**

Participants will be asked the degree of itching they are experiencing on average in the last 24 hours:

Grade Description:

- 0 NONE
- 1 MILD
- 2 MODERATE
- 3 SEVERE

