|                                                                 | 
Each participant will remain at the study site for at least one hour (+30 minutes) to be observed for any immediate reactogenicity complaints associated with the Day 1 treatment.
 

Group	N	Day 1 Observer blind IP or Placebo administered	

MIMIX MAP Dose	

1	15	15 µg	

2	15	7.5 µg	

3	15	Placebo	

 
Participants will be followed for up to 180 days post immunization and evaluated during clinic visits on Study Days 2 (+1), 4 (+1), 8 (±2), 15 (±2), 29 (±2), 57 (±2), 85 (±7), 119 (±7), (final end of study visit) 180 (±7) following vaccination.
 
Participants will be contacted telephonically when an in-person visit is not scheduled through 8 days after treatment and will be assessed for solicited systemic and local adverse reactions and adverse events (AE) through Study Day 8, and solicited erythema and pigmented coloration on Study Days 15, 29, 57 and 180. Unsolicited AEs will be assessed from Study Days 1 through Day 29 after vaccination. Photographs of the treatment sites will be taken at each study visit through Day 57 and then at the end of study visit (Day 180).
                                                                                                                                                                                                                                                                                                                                                                                                                                                                                                                                                                                                                                                                                                                                                                                                                                 | Group          | N | Day 1 Observer blind IP or Placebo administered | MIMIX MAP Dose | 1 | 15 | 15 µg | 2 | 15 | 7.5 µg | 3 | 15 | Placebo |

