| SAFETY ASSESSMENTS | 
On day of vaccination, observe study participants in clinic for a minimum of 1 hour (+ 30 minutes) post-dose as directed by the study physician or designate.
 
Solicitation of local and systemic reactogenicity events will be captured via clinic visits as applicable using standardized grading. Reactogenicity assessment will also include unsolicited complaints.
 
All local and systemic reactogenicity reporting in the 7 days after immunization will be supported via in-person visits and telephonically. Calls are to query for any adverse events using, complete Appendix 1, 2 and the systemic section of Appendix 3, and to determine if an on-site visit is needed.
 
Skin tolerability assessments including pain, induration, tenderness, erythema and edema (Appendix 1: Local Tolerability Scoring) will be carried out on the day of administration (pre-dose, then 1 (<math>\pm 2</math>), 30 (<math>\pm 5</math>) and 60 (<math>\pm 5</math>) minutes post-MAP removal), and on Days 2 (+1), 4 (+1), 8 (<math>\pm 2</math>). Erythema assessments only will be carried out on Days 15 (<math>\pm 2</math>), 29 (<math>\pm 2</math>), 57 (<math>\pm 2</math>) and 180 (<math>\pm 7</math>).
 
Other local tolerability assessments of the MAP application site including bruising, itching, skin flaking and pigmented skin coloration (Appendix 2: Other Local Tolerability Scoring) will be carried out on the day of administration (pre-dose and 60 (<math>\pm 5</math>) minutes post-MAP removal), and on Days 2 (+1), 4 (<math>\pm 1</math>), 8 (<math>\pm 2</math>). Pigmented coloration assessments only will be carried out on Days 15 (<math>\pm 2</math>), 29 (<math>\pm 2</math>), 57 (<math>\pm 7</math>) and 180 (<math>\pm 7</math>).
 |

|                                   |                                                                                                                                                                                                                                                                                                                                                                                                                                           |                               |

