On Day 2 (24 hr post treatment), participants will return to the clinic for an abbreviated physical exam, vital sign measurements, a review of any systemic or local site reactions (skin tolerability and other local tolerability assessments) and for further application site photographs to be taken.

On Day 4 (3 days post treatment), participants will return to the clinic for an abbreviated physical exam, vital sign measurements, a review of any systemic or local site reactions (skin tolerability and other local tolerability assessments) and for further application site photographs to be taken. Blood samples will be collected for hematology and chemistry.

On Day 5, 6 and 7 a phone call will be made to participants to ask about spontaneous adverse events or changes on concurrent medication.

On Day 8 ( $\pm 1$  day) participants will return to the clinic for an abbreviated physical exam, vital sign measurements, a review of any systemic or local site reactions (skin tolerability and other local tolerability assessments) and for further application site photographs to be taken.

On Day 15 (+/- 2 day), participants will return to the clinic for an abbreviated physical exam, vital sign measurements, for erythema ([Appendix 1: Local Tolerability Scoring](#)) only and pigmented coloration assessments ([Appendix 2: Other Local Tolerability Scoring](#)) only and for further application site photographs to be taken.

On Day 29 (+/- 2 day) participants will return to the clinic for an abbreviated physical exam, vital sign measurements, for erythema ([Appendix 1: Local Tolerability Scoring](#)) only and pigmented coloration assessments ([Appendix 2: Other Local Tolerability Scoring](#)) only and for further application site photographs to be taken. Blood samples will be collected for hematology, biochemistry and immunogenicity analysis.

On Day 57 (+/- 4 days), participants will return to the clinic for additional application site photographs, an abbreviated physical exam, vital sign measurements and for erythema ([Appendix 1: Local Tolerability Scoring](#)) only and pigmented coloration assessments ([Appendix 2: Other Local Tolerability Scoring](#)) only. Blood samples will be collected for immunogenicity analysis.

On Day 85 (+/- 7 days), participants will return to the clinic for an abbreviated physical exam and vital sign measurements. Blood samples will be collected for immunogenicity analysis.

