The MIMIX MAP will be administered to the volar forearm on Study Day 1 by study personnel that have the appropriate training and are listed on the Delegation of Authority log. Prior to treatment, the forearm region of the arm must be examined, marked with indelible ink, photographed and cleaned. For the volar forearm, the site of the application must be an area of skin between ~ 4 and 8 cm below the elbow joint.

Application sites will be selected to be free from sores, scarring, blemishes, moles, tattoos, skin conditions, sunburn, heavy hair, redness or coloration which might interfere with the detection of local reactions. If possible, the non-dominant arm of the subject should be used for administration of treatment. Please refer to the VX-103-01 Instructions for Use for additional detail.

All MAP Cartridges must have been removed from 4°C storage by the Study Pharmacist and allowed to equilibrate to room temperature for at least one hour prior to opening the primary pouch, and used within 3 hours of removing from 4°C storage. Once the primary pouch has been opened the MAP must be applied within 15 minutes (+5).

MIMIX MAPs will be applied using the separate spring-powered applicator described in Section 1.2 Vaccine Design following the MIMIX MAP System use sequence shown in Figure 5 and as outlined in the Instructions for Use document Briefly, the MAP Cartridge is loaded onto the applicator by pushing the applicator directly into the open tray and between the snap hooks of the MAP Cartridge. The snap hooks are used to attach the MAP Cartridge to the applicator and to hold the Cartridge in place for MAP delivery. The loaded applicator must be held perpendicular to and just touching the skin of the application site with the arm supported.

The top of the applicator is pressed downward to apply the MAP. Following MAP deployment, the MAP Applicator and Cartridge are immediately removed from the skin, returned to the original Applicator shipping pouch, then to the original Applicator box provided by Vaxess and retained. The patch will remain on the skin for a minimum of 5 minutes and no longer than 10 minutes. The MAP is removed by study staff using gloved fingers, by gently tensioning the skin around the patch with one hand, whilst pulling the MAP directly up and away from the skin with the other hand. Following removal, the MAP should be discarded.

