After the MAP has been removed, skin tolerability assessments ([Appendix 1: Local Tolerability Scoring](#)) including pain, induration, tenderness and erythema will be assessed 1 (±2), 30 (±5) and 60 (±5) minutes post-MAP removal. Other local tolerability assessments ([Appendix 2: Other Local Tolerability Scoring](#)) including bruising, itching, skin-flaking and pigmented coloration will be assessed 60 (±5) minutes post-MAP removal.

If erythema, bruising or induration  $\geq 1$  cm around the treatment site is present, the maximum diameter will be recorded.

The MAP application site will be photographed with the study specific iPhone 1 ( $\pm 2$ ), 30 ( $\pm 5$ ) and 60 ( $\pm 5$ ) minutes post-MAP removal and with the iPhone attached to the study specific DermLite Imaging system 60 ( $\pm 5$ ) minutes post-MAP removal. Please refer to the Imaging Instructions document for additional details.

During the follow up visits, tolerability assessments, photographs of the MAP application site and blood samples will be taken for safety and immunogenicity assessments per the Assessment Schedule [Table 5](#).

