#### **12.4.1 Definition of primary endpoint(s)**

All safety data, including vital signs, laboratory parameters, AE, local and systemic reactogenicity events, physical exams are considered primary endpoints.

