### **Application Site Visibility**

Pigmented (melanin) coloration of the treatment area will be assessed following loss of erythema:

Grade Description:

- 0 Pigmented area <1 cm
- 1 MILD Pigmented area  $\geq$ 1 cm and slightly visible
- 2 MODERATE Pigmented area  $\geq$ 1 cm, noticeable but not clearly defined
- 3 SEVERE Pigmented area  $\geq$ 1 cm and very clearly defined

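### The itching item asks for a 24-hour average but is given 60 minutes after patch removal, so that one score mostly covers time before dosing and tends to under-record acute itching

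*Protocol*

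**What the plan says.** The itching item in Appendix 2 reads "Participants will be asked the degree of itching they are experiencing on average in the last 24 hours", graded 0 (none) to 3 (severe). No other recall period is given for any timepoint. The skin flaking item that follows it has no look-back at all.

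The synopsis (Safety Assessments) says that the Appendix 2 assessments "will be carried out on the day of administration (pre-dose and 60" (±5) minutes after MAP removal. Section 6.1.1 repeats the post-dose timing: other local tolerability assessments "including bruising, itching, skin-flaking and pigmented coloration will be assessed 60 (±5) minutes post-MAP removal". On wear time the same section says: "The patch will remain on the skin for a minimum of 5 minutes and no longer than 10 minutes".

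The next itching assessment is at the Day 2 clinic visit. Section 3 describes it thus: "On Day 2 (24 hr post treatment), participants will return to the clinic for an abbreviated physical exam", with local tolerability scoring included. The synopsis (Study Design) gives the window: participants are "evaluated during clinic visits on Study Days 2 (+1), 4 (+1), 8 (±2").

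On the status of these data, Section 12.4.1 states: "All safety data, including vital signs, laboratory parameters, AE, local and systemic reactogenicity events, physical exams are considered primary endpoints". The synopsis (Endpoint Parameters) tabulates, for each solicited event, the proportion of participants in each group with any non-zero report, and compares groups by Fisher's exact test.

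A related item in Appendix 2, application site visibility, says: "Pigmented (melanin) coloration of the treatment area will be assessed following loss of erythema". It is scheduled at the same 60-minute timepoint and on Days 2, 4 and 8.

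**The concern.** The recall period and the assessment time do not fit each other. About an hour after application, a question about the last day is mainly a question about the time before treatment. It also covers almost the same hours as the pre-dose score with which it would be compared.

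Local reactogenicity is part of the primary endpoint, and this is a first-in-human study of a skin patch, so itching soon after application is of direct interest. The planned summary turns on whether a score is zero or not. A wording that pulls true mild or brief itching towards zero therefore acts on the quantity being tabulated. With 15 participants per arm, one misclassified participant moves an arm's 60-minute proportion by 1/15 = 6.7 percentage points.

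Appendix 1, which is scored at 1, 30 and 60 minutes, has no itching item, so it does not fill the gap. The unsolicited adverse event collection is a weak substitute, because note m to Table 5 describes it as covering events outside the solicited appendices, and itching is inside them.

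**Working it through.** The protocol gives no figure on this point, so there is nothing to reproduce. The check is direct arithmetic.

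**Inputs**
- Recall period: 24 h = 1,440 min (Appendix 2, Itching).
- Wear time: 5 to 10 min (Section 6.1.1).
- Assessment: 55 to 65 min after removal (Section 6.1.1; synopsis, Safety Assessments).
- Day 2 visit: nominally 24 h after treatment (Section 3), window +1 day (synopsis), so up to about 48 h.

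**Share of the recall period after application**
- Post-application time = wear time + time since removal.
- Shortest: 5 + 55 = 60 min; 60/1,440 = 4.2%.
- Longest: 10 + 65 = 75 min; 75/1,440 = 5.2%.
- Share before dosing: 94.8% to 95.8%, which is 1,365 to 1,380 min. If the pre-dose score is taken just before application, all of these minutes also lie in its recall period.

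**What a literal average would give**

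Assume no itching before application, constant itching of grade g afterwards, and grades treated as numbers. The average is g × (post-application time)/1,440.

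| Constant grade since application | Average at 60 min | Average at 75 min |
|---|---|---|
| 1 | 0.042 | 0.052 |
| 2 | 0.083 | 0.104 |
| 3 | 0.125 | 0.156 |

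All of these are nearer to 0 than to 1. For grade 3 itching to average 0.5, it would have to last 0.5/3 × 1,440 = 240 min within the recall period. At most 75 min are available.

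**Does Day 2 recover the first 75 minutes?**
- Visit at 24 h: the recall period contains all 75 min, but spread over 1,440. Grade 3 itching confined to those 75 min still averages 0.156.
- Visit at 25 h 15 min or later, and so at 48 h: the recall period contains none of them.
- Itching that continues through the first day, or on to the visit, is recorded in either case.

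**The case against.** The strongest reply is that the item is a four-category verbal self-report, not a computed mean. The fractional averages above treat ordinal labels as interval numbers and suppose that participants count their symptom-free hours before dosing. The question is also phrased in the present tense, so a participant with an itching forearm may well answer for that moment. This stands. It rules out the claim, which a reader might infer from the table, that the 60-minute result cannot detect acute itching or must look benign in every arm. What remains is an ill-defined time base at that timepoint, with a tendency towards under-recording among those who answer as asked.

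Second, the item is repeated at Day 2, Day 4 and Day 8 and in the calls on Days 5 to 7. If the non-zero tabulation is read at participant level, anyone with itching at a later contact is counted anyway. This also stands, and it narrows the loss to brief itching early on Day 1.

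Third, participants are observed for at least an hour, unsolicited complaints are part of the reactogenicity assessment, and the investigator reviews reported events before discharge. Marked itching would probably be noticed, although it might lack an Appendix 2 grade.

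Fourth, all three arms wear a patch and get the same question. The wording can dilute a difference between arms, but the documents give no reason to expect it to favour one arm.

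On pigmentation, the reference to loss of erythema can be read as a condition for scoring, and the eCRF coding is not visible. Erythema is graded at the same visits, so the affected records could be identified in analysis. A reader might infer that early pigmentation zeros are contaminated, and more so in the more reactive arms; the documents do not establish that.

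**Conclusion.** The mismatch is real and limited. At the 60-minute assessment 94.8% to 95.8% of the stated recall period precedes dosing, whatever the allowed timing, and no other text in the protocol sets a different period. Under-recording follows for participants who answer as asked and had no itching beforehand. For those who report current itching, the score is usable in itself but not comparable with the others. How participants would divide between the two cannot be known from the protocol.

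The effect is on one item at one timepoint within the primary reactogenicity data of a descriptive phase 1 study. Persistent itching is captured from Day 2 on. Short-lived itching in the first hours is the part at risk, most of all when the Day 2 visit is late. It merits correction because the remedy is nearly free and the Day 1 answer cannot be collected again later.

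The pigmentation timing is a secondary point. The minipig studies summarised in Section 8.4.4 showed transient erythema that cleared, returned and resolved by 28 days, so erythema at the early visits is foreseeable. Whether any score would be wrong depends on coding that is not shown.

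**What to change.** In Appendix 2, give the itching item a recall period that fits each timepoint:
- pre-dose: itching now;
- 60 minutes after removal: worst itching since the MAP was applied;
- Day 2 onwards: the 24-hour recall as it stands.

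The whole recall period at 60 minutes then follows application. The change needs revised wording in the appendix and the matching eCRF field, with no added visit or procedure, and has to be in place before dosing to be of use. The small downside is that Day 1 scores have a different recall period from later days, so tables of itching over time should say so.

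Optionally, add a code to the pigmentation item for a site that cannot be assessed because erythema is present, and leave such records out of that visit's denominator. This prevents them from being entered as grade 0.

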### **Skin Flaking**

Participants will be asked the amount of skin flaking of the treatment area they are experiencing:

Grade Description:

- 0 NONE
- 1 MILD
- 2 MODERATE
- 3 SEVERE

### **Application Site Visibility**

Pigmented (melanin) coloration of the treatment area will be assessed following loss of erythema:

Grade Description:

- 0 Pigmented area <1 cm
- 1 MILD Pigmented area  $\geq$ 1 cm and slightly visible
- 2 MODERATE Pigmented area  $\geq$ 1 cm, noticeable but not clearly defined
- 3 SEVERE Pigmented area  $\geq$ 1 cm and very clearly defined

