| Adverse Event Collection (Unsolicited) m                                                    | X | Days 1-29  |   |   |   |   |   |   |   |     |     |     |   |   |     |  |   |
| SAEs, MAEs and NOCMCs                                                                                  |   | Days 1-180 |   |   |   |   |   |   |   |     |     |     |   |   |     |  |   |
| Serum for Serological Immunogenicity Assays: HAI Titers                                                |   | X          |   |   |   |   |   |   |   |     | X   | X   | X | X | X   |  | X |
| Serum for Exploratory Endpoints: HAI Drifted Strain; Anti HA IgG, Anti- Fibroin IgG, IgE and MN Titers |   | X          |   |   |   |   |   |   |   |     | X   |     |   |   | X   |  | X |
| Safety Telephone Contact n                                                                  |   |            |   |   |   |   |   | X |   |     |     |     |   |   |     |  |   |

\*Erythema assessments only from [Appendix 1: Local Tolerability Scoring](#)  
\*\*Coloration assessment only from [Appendix 2: Other Local Tolerability Scoring](#)

- a. The signed informed consent of the subject must be obtained before study participation.
- b. Record demographic data such as year of birth, sex, race (ethnicity and geographic ancestry) in the subject’s eCRF
- c. Obtain the subject’s medical history by interview and/or review of the subject’s medical records and record any pre-existing conditions or signs and/or symptoms present in a subject prior to the first study vaccination in the eCRF.
- d. Perform a physical examination of the subject, including assessment of oral body temperature and resting vital signs: systolic/diastolic blood pressure, heart rate and respiratory rate after at least 5 minutes of rest, pulmonary auscultation. Collected information needs to be recorded in the eCRF. Any findings from the(se) physical examination(s) need to be recorded in the subject’s medical record, in the medical history screen of the eCRF or reported as an AE or SAE, as applicable, if they meet the protocol definition of AE or SAE. Treatment of any abnormality observed during physical examination has to be performed according to local medical practice outside this study or by referral to an appropriate specialist. After the screening visit, an abbreviated physical exam should be performed at each visit until the final study visit.

- 

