#### **8.4.4 Appropriateness of safety measurements**

The porcine model has been extensively used as a model for studying human skin responses to medical devices. Compared to other common animal models, the epidermis and dermis of the pig has a thickness that is most similar to humans. The pig epidermis ranges from 30 to 140  $\mu\text{m}$ ; human skin ranges from 50 to 120  $\mu\text{m}$ . In addition, the skin of the pig is more firmly attached to the underlying structures as seen in humans ([Abdullahi et al., 2014](#)). Further, pig skin heals through re-epithelialization, unlike mice, rats, and other rodents whose skin heals through contraction. These features make the minipig a particularly useful model for evaluating the local and systemic effects of MIMIX MAPs as well as a useful model for determining if the MIMIX tip material will ultimately be absorbed or ejected and the likely timeline for this event in humans. Vaxess has carried out a pilot evaluation of MAP tolerability and tip persistence and a pilot repeat-dose systemic toxicology study in the Göttingen minipig model. We find that the minipig develops robust immune responses to the VX-103 vaccine antigen. In both pilot studies the results showed transient erythema and edema at the MAP application site that resolved by 28 days post MAP application. The erythema and edema reported, characteristically resolves in the first several days, then reappears and resolves by 28 days. No detectable adverse safety findings were reported. The pilot implantation effects study provides evidence that, by day 90, tip material for MIMIX FLU test articles is absorbed or ejected, there is no longer inflammation, and tissue has been restored to normal structure.

In sum, no adverse systemic events have been reported to date in our preclinical safety studies and local reactogenicity has been limited to transient erythema and edema. These data have been used to inform the design of the Phase 1 clinical trial.

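### Pigmentation is to be scored after erythema has gone, yet it is scheduled at fixed times when the site may still be red, and the scale has no entry for a red site

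*Protocol*

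**What the plan says.** The pigmentation item in Appendix 2 (Application Site Visibility) opens: "Pigmented (melanin) coloration of the treatment area will be assessed following loss of erythema". Its grades run from 0, defined as "Pigmented area <1 cm", to 3. There is no code for a site that cannot be assessed, and the protocol does not say what counts as loss of erythema.

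The schedule carries no such condition:

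- Section 6.1.1, on Day 1: "bruising, itching, skin-flaking and pigmented coloration will be assessed 60 (±5) minutes post-MAP removal".
- Synopsis, Safety Assessments: "Other local tolerability assessments of the MAP application site including bruising, itching, skin flaking and pigmented skin coloration" are due before dosing, at 60 minutes and on Days 2, 4 and 8. Pigmentation alone follows on Days 15, 29, 57 and 180.
- Section 3, for each of Days 2, 4 and 8: "a review of any systemic or local site reactions (skin tolerability and other local tolerability assessments".
- Table 5 restricts Appendix 2 at the later visits by a footnote that begins "Coloration assessment only from". The earlier visits therefore carry the full set of items.

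Erythema is graded under Appendix 1 on Day 1, on Days 2, 4 and 8, and again on Days 15, 29, 57 and 180. Section 8.4.4 reports that in minipigs the erythema and edema "characteristically resolves in the first several days, then reappears and resolves by 28 days".

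Section 12.4.1 counts local reactogenicity among the primary endpoints. The Synopsis tabulates, for each solicited event, the proportion of participants per group with a score above zero and compares groups by Fisher's exact test. Section 12.4.2 adds summaries by treatment group, ethnicity and visit where these are judged relevant.

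**The concern.** A rater facing a red site at a scheduled visit cannot obey both instructions. Appendix 2 says the time to score has not come, while the schedule says a score is due now. The form offers only 0 to 3, so three outcomes are possible: a 0, a blank, or a score in which redness passes for pigment. With up to three sites, different raters may settle on different habits.

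Redness is also a possible effect of treatment. If one arm is red more often, the share of its pigmentation scores that is missing or wrong differs from the other arm's. The tabulation of scores above zero makes this worse in one respect: a 0 entered because the site could not be judged looks the same as a 0 entered because no pigment was seen. If the denominator is everyone in the group, a blank has the same effect. At stake are the early by-visit pigmentation rates within a primary endpoint of a first-in-human patch study.

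**Working it through.** The protocol gives no pigmentation or erythema rate, so there is no stated figure to reproduce. The check has two parts.

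**1. The instructions side by side**

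| Time | Pigmentation due? | Erythema graded then? | Could the site be red? |
|---|---|---|---|
| 60 minutes | Yes (Synopsis, 6.1.1, Table 5) | Yes | Yes, soon after removal |
| Days 2, 4, 8 | Yes (Synopsis, 3, Table 5) | Yes | Possible; minipig erythema cleared within several days |
| Days 15, 29 | Yes, this item alone from Appendix 2 | Yes | Possible; minipig erythema reappeared and cleared by 28 days |
| Days 57, 180 | Yes, this item alone from Appendix 2 | Yes | Unlikely on the minipig evidence |

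No schedule text waives or repeats the erythema condition. The conflict is in the protocol itself and needs no further document to establish it.

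**2. What handling does to a by-visit rate (all rates assumed)**

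Let r be the share of an arm still red, p_red and p_clear the true pigmentation rates in red and non-red participants, and n = 15 per arm (Table 2).

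- True rate = r × p_red + (1 − r) × p_clear
- Red sites scored 0, or blank counted as no report = (1 − r) × p_clear
- Redness scored as pigment = r + (1 − r) × p_clear
- Red sites left out of the denominator = p_clear, with n × (1 − r) assessed

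*Pigmentation independent of redness, true rate 40% in both arms.* The comparison arm has r = 20%; the more reactive arm has r = 40%, 60% or 80%.

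| r, more reactive vs other arm | Red scored 0 | Redness as pigment | Red left out | Assessed |
|---|---|---|---|---|
| 40% vs 20% | 24% vs 32% | 64% vs 52% | 40% vs 40% | 9 vs 12 |
| 60% vs 20% | 16% vs 32% | 76% vs 52% | 40% vs 40% | 6 vs 12 |
| 80% vs 20% | 8% vs 32% | 88% vs 52% | 40% vs 40% | 3 vs 12 |

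For the middle row: 0.40 × 0.40 = 0.16 against 0.80 × 0.40 = 0.32; and 0.60 + 0.40 × 0.40 = 0.76 against 0.20 + 0.80 × 0.40 = 0.52.

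*Equal redness, r = 20% in both arms.* Scoring red sites 0 gives 32% against 32%. The level falls below 40%, but no difference between arms is created.

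*Red participants pigment more (60% against 20%), r = 60% vs 20%.* The true rates are 0.60 × 0.60 + 0.40 × 0.20 = 44% and 0.20 × 0.60 + 0.80 × 0.20 = 28%. Red scored 0 gives 8% vs 16%, which reverses the order. Red left out gives 20% vs 20%, which hides the difference.

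So the same true data can show a deficit, an excess or nothing, depending on a handling rule that the protocol does not state.

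**The case against.** The strongest reply is that the passages can be read together: the schedule says when Appendix 2 is completed, and the item says when pigmentation applies. A red site is then left unscored, and how a blank enters a table may properly be left to the analysis plan or the completion guidance. On that reading, and if pigmentation is independent of redness, omitting red sites creates no false difference; it only shrinks the denominator. That stands as a sensible reading, but the protocol does not state it, and the form gives a rater no way to record it.

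A second reply is that erythema grades and photographs from the same visits allow red sites to be identified later. This holds only in part. Appendix 1 Grade 0 covers redness below 1 cm, and Section 6.1.1 asks for a diameter only from 1 cm upward. A Grade 0 site may therefore still have been red.

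A reader might go further and infer that the more reactive arm will look less pigmented, or that the comparison with placebo is biased however red sites are handled. The documents do not support that:

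- They give no erythema rates by arm. Placebo is the same patch with the same silk fibroin and Tween 20, lacking only the antigen, so a large contrast in redness cannot be presumed.
- The direction changes with handling, as the working shows.
- In a table of any score above zero over the whole follow-up, a site red on Day 2 and pigmented on Day 29, 57 or 180 still counts.

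Nor does the minipig evidence make every visit from 60 minutes to Day 29 a red one. It describes an interval without erythema between two phases, and it comes from animals.

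**Conclusion.** The contradiction stands. Appendix 2 makes pigmentation scoring follow loss of erythema, the schedule requires the score regardless, and the scale cannot record a site that is still red. Early by-visit pigmentation rates can be distorted if erythema differs between arms, and so can any tabulation that treats 0 or blank as no report.

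The size and direction are not known from the documents. Under the assumed rates above, with equal true pigmentation, the apparent difference runs from 24 points too low (8% vs 32%) to 36 points too high (88% vs 52%) for the more reactive arm, and is zero if red sites are left out. These figures show how far handling matters; they do not predict this trial. Days 57 and 180 are probably little affected, so late pigmentation should still be captured. No sample size or error rate is involved.

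**What to change.** 1. Reconcile the pigmentation item in Appendix 2 with the Synopsis, Sections 3 and 6.1.1 and Table 5, so that one rule governs scheduled visits at which the site is still red.
2. State what loss of erythema means relative to the Appendix 1 grades: no visible redness, or Grade 0, which allows redness below 1 cm.
3. Add a 'not assessable: erythema present' code to the pigmentation item, kept distinct from 0 and from missing.
4. Report, by arm and visit, the number assessable and the pigmentation rate among those assessable.

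The cost is one case report form code and a few lines of text; no visit or sample changes. The downside is a smaller denominator at early visits, and rates among assessable sites can still hide a difference if red sites pigment more or less than others. Showing the number assessable lets the reader see this. There is no need to restrict the comparison between arms to Days 57 and 180 or to reduce the early scores to listings, since that would set aside valid scores from sites that are not red.
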